## Abstract

**Background:**

In the US, Hispanic women have a higher incidence of, and mortality from, cervical cancer than non-Hispanic white women. The reason for this disparity may be attributable to both low rates of screening and poor adherence to recommended diagnostic follow-up after an abnormal Pap test. The 'Cervical Cancer Screening and Adherence to Follow-up Among Hispanic Women' study is a collaboration between a research institution and community partners made up of members from community based organizations, the Yakima Valley Farm Workers Clinic and the Breast, Cervical, and Colon Health Program of the Yakima District . The study will assess the efficacy of two culturally-appropriate, tailored educational programs designed to increase cervical cancer screening among Hispanic women, based in the Yakima Valley, Washington, US.

**Methods/design:**

A parallel randomized-controlled trial of 600 Hispanic women aged 21–64, who are non-compliant with Papanicolau (Pap) test screening guidelines. Participants will be randomized using block randomization to (1) a control arm (usual care); (2) a low-intensity information program, consisting of a Spanish-language video that educates women on the importance of cervical cancer screening; or (3) a high-intensity program consisting of the video plus a *‘promotora’* or lay-community health educator-led, home based intervention to encourage cervical cancer screening. Participants who attend cervical cancer screening, and receive a diagnosis of an abnormal Pap test will be assigned to a patient navigator who will provide support and information to promote adherence to follow-up tests, and any necessary surgery or treatment. Primary endpoint: Participants will be tracked via medical record review at community-based clinics, to identify women who have had a Pap test within 7 months of baseline assessment. Medical record reviewers will be blinded to randomization arm. Secondary endpoint: An evaluation of the patient navigator program as a method to improve adherence and reduce time to follow-up among participants who receive an abnormal Pap test result. An additional secondary endpoint is the cost-effectiveness of the two different intensity intervention programs.

**Discussion:**

This culturally sensitive intervention aims to increase compliance and adherence to cervical screening in a Hispanic population. If effective, such interventions may reduce incidence of cervical cancer.

**Trial registration:**

NCT01525433

## Background

Cervical cancer screening detects pre-cancerous changes in the cervix, such as cervical intraepithelial neoplasia (CIN) or cervical dysplasia. Introduction of the Papanicolau (Pap) test screening programs to women in all populations reduces cervical cancer rates by 60–90 percent within 3 years of implementation, with the reduction of mortality and morbidity consistent across populations [1,2]. In the US, the US Preventative Task Force guidelines for Pap testing are every 3 years for routine screening by women over the age of 21, or from three years after the age of initiation of sexual activity, whichever is earlier [3].

Hispanic women in the US have the highest cervical cancer incidence with an age-adjusted incidence of 12.5 cases/100,000 women for 2004–2008, compared to an incidence of 7.0 in the non-Hispanic white population [4]. Mortality from cervical cancer is also higher among Hispanics compared to non-Hispanic whites (estimates for age-adjusted U.S. mortality rates for 2008: 2.9 per 100,000 vs. 2.1 per 100,000) [4]. The disproportionate burden of cervical cancer among Hispanic women is thought to be attributable in part to both low rates of screening and poor adherence to recommended diagnostic follow-up after an abnormal Pap test. Data from the National Health Interview Survey show that 74.6% of Hispanic women had a Pap test in the past three years compared to 81.4% of non-Hispanic whites [5]. Similarly, Hispanic non-adherence with recommended follow-up has been reported in several regional studies to range from 20 to 90% [6,7].

Sociodemographic factors associated with non-adherence to cervical cancer screening in this population include low income, lack of health insurance, limited access to healthcare services, lack of clinician recommendation, length of residency in the United States, limited English language proficiency, acculturation, and lack of awareness of risks associated with non-participation in cervical cancer screening programs [8-11].

The aims of the Cervical Cancer Screening and Adherence to Follow-up Among Hispanic Women study are threefold: (1) to determine the effect of two different intensity, culturally appropriate information based interventions on Pap test utilization, vs. control; (2) to determine whether a patient navigator program can improve adherence to follow-up after a diagnosis of an abnormal Pap test, in a sample of Hispanic women in Yakima and Franklin counties of Washington (WA) State, US; and (3) to assess the cost-effectiveness of each of the intervention programs.

The study will be implemented with the aid of the two community based partners, the Yakima Valley Farm Workers’ Clinic (YVFWC) which operates a network of 13 federally qualified health center clinics in Eastern Washington specializing in the delivery of primary care services to low-income Latinos; and the Breast, Cervical, and Colon Health Program of the Yakima District (BCCHP), a federally funded aid program, administered through the Washington State Department of Health, which provides assistance and resources for women to undergo Pap tests, and for women who receive a diagnosis of an abnormal Pap test.

BCCHP and YVFWC will work with the study investigators to identify women who are non-compliant with Pap testing to monitor uptake of Pap test screening among randomized women via medical record review, and to develop and pilot test a patient navigator program to improve adherence and reduce time to follow-up after an abnormal Pap test.

To aid with issues regarding cultural relevance, a community advisory board was appointed and regular meetings are scheduled between the investigators and community members.

## Methods/design

The ‘Cervical Cancer Screening and Adherence to Follow-up Among Hispanic Women’ study is a parallel randomized controlled trial with participants randomized into a control or usual care arm; a high intensity intervention *‘Promotora’* plus video arm; or a low-intensity ‘video’ only arm (Figure 1). The interventions are behavioural and information based, and are designed to educate participants about the importance of cervical cancer screening, and to encourage women to obtain screening. The study will be conducted in Yakima Valley, WA, US, and has been approved by the Institutional Review Board (IRB) of the Fred Hutchinson Cancer Research Center.

**Figure 1 F1:**
[figure not shown]
CONSORT diagram.

### Setting

In Washington State, much of the Hispanic population is concentrated in Yakima County, and Hispanics are the fastest growing population in the region, having increased by 37% between the 2000 and 2010 census, and the percentage of Hispanics is 45% of the population [12].

### Participants

The study aims to recruit 600 Hispanic women, who have been seen by a community health partner clinic (YVFWC) within the past 5 years, and who are out of compliance with current recommendations for Pap test screening, i.e., have not had a Pap test within the previous 3 years. Eligible women will be between 21 – 64 years of age as is consistent with guidelines, without a prior hysterectomy. Participants may be English or Spanish speakers and are resident in the Yakima Valley Washington, USA.

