### Recruitment of participants

We will use recruitment strategies that were successfully used in our other studies involving community based clinics [13]. Details of Hispanic females who are eligible, who have been seen in the YVFWC clinics in the past five years, and who are non-compliant with cervical cancer screening recommendations will be extracted from computerized patient records. Eligible women will be invited to participate in the study by the YVFWC. Interested women will be told that they will be randomized to one of three arms in the project. The women will be assured that refusal to participate will not have any implications on the ability to receive care at the clinic. Women will be asked to sign an informed consent to participate in the project, and to sign a HIPAA authorization for release of medical record information for the purposes of verifying their use of cervical cancer screening. Once consent is obtained, a study staff member will telephone or go to the home of the participant to complete a baseline survey. The baseline questionnaire includes items on cervical cancer screening knowledge and attitudes as well as intention to be screened, acculturation, and sociodemographic variables.

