### Randomization

Participants will be allocated to the intervention or control arms via a computerized program. A randomized block design assuring that randomization is balanced after every 15 participants will be used to ensure equal distribution across study arms. The randomization sequence was generated by a statistician who is not involved with the study. Medical record reviewers will be blinded to the randomization status of the participants.

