### Interventions

Following baseline assessment, the participant will be randomized to control arm (usual care), mailed video only, or video plus *promotora* outreach, as described below.

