#### Control arm

Participants who are allocated to the control arm (‘Usual Care’) will not receive any motivational messages or intervention materials from study staff. Usual care entails any information on the importance of regular Pap tests for cervical cancer risk reduction provided routinely by clinic staff to all women at community clinics.

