#### Low intensity intervention (video)

Participants will be mailed a culturally-appropriate Spanish-language video with information and encouragement to undergo cervical cancer screening, information about resources to pay for screening, and other practical assistance such as resources for transportation. This intervention consists of a 13 minute video presentation of three different generational women talking in Spanish about their experiences and concerns for cervical cancer screening in the form of a “novela” or soap opera. The video has English subtitles for monolingual English-speaking participants. The video was developed as part of the ‘Ayudando a Las Mujeres con Informacion, Guia y Amor para su Salud’ (AMIGAS) intervention, which consisted of a lay community health educator or *promotora de salud*-(*promotora)* led in-home education session, and a video presentation. The culturally appropriate, theoretically-based curriculum was developed using a community-based participatory research approach, with the aim of increasing the uptake of cervical screening for Hispanic women living along the U.S./Mexican border [14].

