#### High intensity intervention (video plus *promotora* outreach)

In this arm, women will receive a high-intensity intervention that includes *promotora*-led in-home education session. The educational session will include the culturally-appropriate video (as used in the low intensity intervention) [14], a “promise sheet” (i.e., a sheet that a woman signs to indicate what she will do next, such as thinking about having a Pap test, making an appointment), and a resource sheet which lists resources such as contact information for community resources for transportation, childcare, and other potential barriers for successful attendance at clinic. The *promotora* will have the opportunity to have a conversation about cervical cancer screening and directly schedule a Pap test for women through the clinic. For women who are not yet ready to schedule a Pap test, the *promotora* will make a telephone call to the woman two weeks later to review the action steps, and assess readiness to schedule a Pap test.

A *promotora* will be recruited by YVFWC from the community and will be provided with an initial training session lasting three days, which addresses procedures for approaching households and delivering the intervention, cervical cancer screening facts and tracking and documentation procedures. Other studies indicate *promotora* outreach to be a successful approach for Hispanic women [15-18].

Both the video and *promotora* led intervention are part of an educational curriculum created to increase cervical cancer screening in Hispanic women; the curriculum is based in Social Cognitive Theory (SCT). Definitions of social cognition vary, but central to the theory is that people’s social behavior can be understood by examining their beliefs about their behavior in a social context; and that people learn not only from their own experiences, but by observing the actions of others. According to SCT, three main factors, self-efficacy, goals and outcome expectancies, affect the likelihood of changing a health behavior [19,20].

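### With individual randomization and no household limit, women who share a home can be split across arms of a home-delivered intervention; one woman per address is a cheap safeguard

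*Protocol article*

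**What the plan says.** Four parts of the protocol article bear on this.

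- **Entry.** Participants gives the age and hysterectomy criteria: "Eligible women will be between 21 – 64 years of age as is consistent with guidelines, without a prior hysterectomy". It also requires a clinic visit in the past 5 years and no Pap test in the past 3. Recruitment of participants draws these women from computerized clinic records and continues: "Eligible women will be invited to participate in the study by the YVFWC". Neither section limits entry to one woman per home.
- **Allocation.** Interventions makes the individual the unit: "Following baseline assessment, the participant will be randomized to control arm (usual care), mailed video only, or video plus" promotora outreach. Randomization adds: "A randomized block design assuring that randomization is balanced after every 15 participants will be used to ensure equal distribution across study arms". No household cluster or stratum is named.
- **Delivery.** In the low-intensity arm, "Participants will be mailed a culturally-appropriate Spanish-language video". In the high-intensity arm, "women will receive a high-intensity intervention that includes *promotora*-led in-home education session", and that session uses the same video.
- **Control.** Women in this arm "will not receive any motivational messages or intervention materials from study staff".

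Sample size and Statistical analysis plan chi-square tests of each intervention arm against control. They make no allowance for exposure across arms.

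**The concern.** The age range is wide enough for a mother, an adult daughter or sisters at one address each to qualify. All candidates come from one clinic network's records. If two of them enrol, the stated rules can put one in the control arm and the other in an arm whose material reaches the shared home.

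The intervention is also meant to work socially. The article bases the curriculum on Social Cognitive Theory, in which people learn partly from watching others, and the video portrays women of three generations. A relative in the same house is therefore a plausible audience.

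Exposure of this kind raises screening among controls. Where the co-resident receives the promotora visit, it also raises screening among video-only women. The low-versus-control contrast is one of two primary tests and has little spare power at the upper end of the assumed rates. The low-versus-high comparison is blurred as well. No later analysis can remove an exposure that has already taken place.

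**Working it through.** **Inputs from the article.** 600 women, 200 per arm; 10% loss; 180 per arm for power; significance level 0.025 per test (two-sided assumed). Assumed compliance is 0.15 to 0.30 (control), 0.30 to 0.45 (low) and 0.45 to 0.60 (high), with steps of at least 0.15.

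**Inputs not in the article (assumptions).** h is the share of participants who live with one other participant. Transfer is the part of the co-resident's intervention effect that an exposed woman gains.

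**1. The plan's own figures.** 180 / (1 − 0.10) = 200 per arm, and 3 × 200 = 600. 2 × 0.025 = 0.05. These reproduce. The article states no power value, so it is computed here:

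power = Φ{ [d√n − z√(2p̄(1−p̄))] / √(p₁(1−p₁) + p₂(1−p₂)) }, with n = 180, z = 2.2414 and p̄ the mean of p₁ and p₂.

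- 0.15 versus 0.30: (2.0125 − 1.3237) / 0.5810 = 1.186, power 88.2%.
- 0.30 versus 0.45: power 76.0%.
- High versus control (0.15 versus 0.45, 0.30 versus 0.60): above 99.9%.

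**2. Chance of a split.** Under 1:1:1 allocation, a woman's co-resident is in a different arm with probability 2/3. If both fall in the same block of 15, it is 10/14 = 71%. For a control, a different arm always means an active arm.

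**3. Dilution with full transfer of the video effect.** The control rate rises by h × 2/3 × 0.15 = 0.10h.

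| h | Women (homes) of 600 | Rise in control rate | Low vs control difference | Power, 0.15 vs 0.30 | Power, 0.30 vs 0.45 |
|---|---|---|---|---|---|
| 0 | 0 | 0 | 0.150 | 88.2% | 76.0% |
| 2% | 12 (6) | 0.002 | 0.148 | 87.2% | 74.7% |
| 5% | 30 (15) | 0.005 | 0.145 | 85.4% | 72.7% |
| 10% | 60 (30) | 0.010 | 0.140 | 82.3% | 69.2% |
| 20% | 120 (60) | 0.020 | 0.130 | 75.0% | 61.6% |

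Example at h = 5%, 0.155 versus 0.30: (0.145 × 13.416 − 2.2414 × 0.5929) / 0.5839 = 1.056, power 85.4%.

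Half transfer at h = 5% gives 86.9% and 74.4%. High versus control stays above 99.9% in every row.

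**4. If a promotora co-resident passes on her whole effect (+0.30).** Controls rise by h × (1/3 × 0.15 + 1/3 × 0.30) = 0.15h. Video-only women rise by h × 1/3 × 0.15 = 0.05h. The low-versus-control difference still shrinks by 0.15h − 0.05h = 0.10h, as in the table. The low-versus-high difference shrinks by 0.05h. If controls gained in this way but video-only women did not, power at h = 10% would be 78.8% and 65.5%.

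**The case against.** The strongest reply is that the point rests on silence. The quoted eligibility sentence contains no error, the article is a condensed account, and a household check could sit in the full protocol or field procedures. That possibility stands. However, the article does state the entry rules, the unit of allocation and the mode of delivery, and taken together they allow co-residents to be split.

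The second reply concerns size, and it stands in full. Nothing in the article supports any value of h. Both women at an address must meet every criterion, consent and be among the 600; h = 20% would need 60 such homes. Full transfer of the video effect is an upper bound on what a shared video can do. A loss of 1 to 3 points of power is quite possible, and the 76.0% starting value owes nothing to households.

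A reader might also infer three stronger things, which the document does not support:

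- **A conflict with the Control arm section.** That section bars only messages and materials coming from study staff. A video shared by a relative does not breach it.
- **Invalid chi-square tests because co-residents' outcomes are correlated.** Under individual allocation, same-arm pairs and split pairs are expected equally often in any two-arm contrast, so their covariances cancel. Simulation at h = 20% with within-pair correlation 0.3 or 0.5 gave a type I error of about 0.025 at nominal 0.025.
- **Serious loss for both primary tests.** The high-versus-control estimate is also pulled toward zero, but its power is hardly touched.

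**Conclusion.** The point holds as a minor weakness of design. The rules as stated let co-resident women be split across arms of an intervention that reaches the home, and any resulting exposure biases toward no effect. The low-versus-control test and the low-versus-high comparison are the ones that matter.

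With two-participant homes and full video transfer, the loss of low-versus-control power runs from about 1 point at h = 2% to 13 or 14 points at h = 20%. The true h and the true transfer are both unknown, so these figures show a range and are not an estimate. If few homes supply two participants, the effect is negligible. The reason to act is that prevention is almost free.

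**What to change.** State in Participants and in Recruitment of participants that only one woman per household may enter. Match the clinic record extract on address and, where several eligible women share one, pick one at random before any invitation is sent. The same match shows how many eligible women share an address.

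The cost is one step on an extract already planned and a slightly smaller recruitment pool, with no added visits or staff. The randomization and the planned tests need no change.

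Giving every woman at an address the arm of the first one randomized is not a good substitute. A later woman's arm would be knowable before she consents. It would also create the clustering that individual allocation avoids: in simulation, type I error with the planned chi-square test rose to between 0.028 and 0.034.

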### Recruitment of participants

We will use recruitment strategies that were successfully used in our other studies involving community based clinics [13]. Details of Hispanic females who are eligible, who have been seen in the YVFWC clinics in the past five years, and who are non-compliant with cervical cancer screening recommendations will be extracted from computerized patient records. Eligible women will be invited to participate in the study by the YVFWC. Interested women will be told that they will be randomized to one of three arms in the project. The women will be assured that refusal to participate will not have any implications on the ability to receive care at the clinic. Women will be asked to sign an informed consent to participate in the project, and to sign a HIPAA authorization for release of medical record information for the purposes of verifying their use of cervical cancer screening. Once consent is obtained, a study staff member will telephone or go to the home of the participant to complete a baseline survey. The baseline questionnaire includes items on cervical cancer screening knowledge and attitudes as well as intention to be screened, acculturation, and sociodemographic variables.

### Randomization

Participants will be allocated to the intervention or control arms via a computerized program. A randomized block design assuring that randomization is balanced after every 15 participants will be used to ensure equal distribution across study arms. The randomization sequence was generated by a statistician who is not involved with the study. Medical record reviewers will be blinded to the randomization status of the participants.

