### Sample size

Power is assessed for the primary endpoint, i.e. increased compliance with cervical cancer screening. We assume compliance probabilities will range from 0.15 to 0.30 for usual care, 0.30 to 0.45 for the low-intensity arm, and 0.45 to 0.60 for the high-intensity arm with at least a 0.15 difference between the low intensity and control arms and the low and high intensity arms. Assuming a 10% loss to follow-up these power calculations are based on a sample size of 180 in each of the three arms, assuming two Chi square tests will be conducted; one to compare the low intensity arm to the control arm and one to compare the high intensity arm to the control arm. The overall significance level for the two tests was targeted at 0.05 so that each test is powered with significance level 0.025 to account for the two primary evaluations.

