### Statistical analysis

The primary end-point (Pap test compliance) will be coded as a binary variable. Evaluation of the success of the intervention is based only on Pap test compliance at follow-up. Chi square tests of 2 X 2 tables (compliance Yes/No by arm Control vs. High or Low intensity intervention) will be employed to assess whether intervention arms affects the probability of compliance at follow-up. We will randomize about 600 women (anticipated 200 per arm to each of 3 arms; control, low intensity intervention, high intensity intervention) into the study, which will allow for 10% attrition. Separate analysis will be conducted to compare the high intensity arm to the control arm and the low intensity arm to the control arm, and subsequent analysis will include comparing the low intensity arm to the high intensity arm as well as adjustment of the primary analysis by potential confounding characteristics such as race and age, to account for potential biases in the randomization.

Additional secondary analysis will include evaluating the effect of contact from a patient navigator to women who receive an abnormal Pap smear. All participants seen at the study clinics during the course of the study who receive an abnormal Pap smear (intervention population) will receive a contact from the patient navigator. These women will be compared to women who received an abnormal Pap smear at the same clinics between 180 and 90 days prior to the start of the study when no navigator calls were made (control population) as determined by medical records. The outcome measure will be determination of follow up for an abnormal Pap smear within 90 days of initial contact by the clinic. We will compare length of time from initial diagnosis to attendance at the clinic for recommended follow-up in the participants who have been contacted by the patient navigator, vs. the control population

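### The single fixed, disclosed block of 15 leaves up to about half of allocations correctly guessable by anyone who can follow earlier ones; undisclosed, varying blocks of similar or larger size would be a cheap improvement

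*Protocol article*

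**What the plan says.** Under Randomization, the protocol article gives one balancing rule: "A randomized block design assuring that randomization is balanced after every 15 participants will be used to ensure equal distribution across study arms". Allocation is by a computer program, from a sequence generated by a statistician outside the study. Medical record reviewers are the only people named as blinded.

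The target is stated under Participants ("The study aims to recruit 600 Hispanic women") and under Statistical analysis ("anticipated 200 per arm to each of 3 arms; control, low intensity intervention, high intensity intervention").

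On the order of events, Recruitment of participants says: "Once consent is obtained, a study staff member will telephone or go to the home of the participant to complete a baseline survey". That survey includes an item on intention to be screened. The Interventions section then says: "Following baseline assessment, the participant will be randomized to control arm (usual care), mailed video only", or the video plus promotora outreach.

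What a woman receives shows her arm: nothing from study staff, a mailed video, or a home session with a promotora who "will be recruited by YVFWC from the community".

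**The concern.** With a fixed block, the places still open in a block follow from those already used. Anyone who knows the block length and has followed the earlier allocations can lean towards the right arm as the block fills, and sometimes knows it outright. An independently generated list does not prevent this, because the inference comes from past allocations and not from sight of the list.

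Here the block length is public and delivery is open, so those who deliver the interventions learn allocations as they happen. If the same information reaches whoever decides which consented woman is surveyed and randomised next, a woman thought likely to attend could be brought forward or held back. Readiness to be screened plausibly predicts Pap test completion, the primary outcome. An imbalance created at entry would carry into both comparisons with control, and blinded record review could not undo it. Adjustment is planned as a later analysis, and its named examples are race and age, not intention.

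**Working it through.** **Inputs.** Block of 15 (Randomization); three arms, 200 each (Statistical analysis); 600 women (Participants). *Assumed, not stated:* the guesser sees every earlier allocation in order and knows where blocks begin.

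**The plan's own figures.** Sample size gives 180 evaluable per arm after 10% loss: "Assuming a 10% loss to follow-up these power calculations are based on a sample size of 180 in each of the three arms". 180 / 0.90 = 200 per arm; 3 × 200 = 600; 600 / 15 = 40 complete blocks; 40 × 5 = 200 per arm. These reproduce. The article gives no predictability figure.

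**Average hit rate, fixed 5/5/5 block.** The best strategy is to name the arm with most places left. With remaining places (a, b, c) and t = a + b + c, the expected number of correct guesses obeys

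f(a,b,c) = max(a,b,c)/t + (a/t)·f(a−1,b,c) + (b/t)·f(a,b−1,c) + (c/t)·f(a,b,c−1), with f(0,0,0) = 0.

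f(5,5,5) = 7.46, and 7.46 / 15 = 49.7%, against 33.3% by chance. By position in the block:

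| Place | 1st | 5th | 10th | 14th | 15th |
|---|---|---|---|---|---|
| Hit rate | 33% | 40% | 49% | 64% | 100% |

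**Places known with certainty.** The last k places all belong to one arm with probability 3·C(5,k)/C(15,k). Summing over k = 1 to 5: 1.000 + 0.286 + 0.066 + 0.011 + 0.001 = 1.364 per block. 1.364 / 15 = 9.1%, and 40 × 1.364 = 54.5 of 600 women. At least one arm is ruled out for 3.64 of 15 places (24.2%).

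**Partial sight.** By simulation with block boundaries known, a guesser who sees half of the earlier allocations is right about 40% of the time, and one who sees a third about 38%.

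**Alternatives.** These are simulations of 600 women in which block sizes are drawn at random and boundaries are hidden. The guesser names the least-used arm. Places count as certain for someone who knows which sizes are possible but not their order.

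| Scheme | Hit rate | Certain |
|---|---|---|
| Fixed 15 | 49.7% | 9.1% |
| 6/9/12/15 | about 51.7% | about 1.5% |
| 12/15/18 | about 49.6% | about 1.5% |
| 15/18/21 | about 48.5% | about 1.2 to 1.4% |

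Varying the size removes most of the certainty. Only larger blocks lower the average; exact recursion gives 56.1% for a fixed 6, 53.2% for a fixed 9 and 45.7% for a fixed 30.

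**Illustration of the stakes (all inputs assumed).** Suppose half of the women are keen, and staff can tell this before randomisation.

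- Steering only on certain places: keen women make up 0.5 + 0.5 × 0.091 = 54.5% of the high-intensity arm and 45.5% of control, a gap of about 9 points. If keen women are screened 10 to 30 points more often, the spurious difference is 0.9 to 2.7 points.
- Steering at every place where the remaining high-intensity and control places differ: 65% against 35%, so about 3 to 9 points.

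For scale, the smallest planned difference between low intensity and control is 15 points. These are scenarios, not predictions.

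**The case against.** The strongest reply is that the article does not describe the conditions needed for steering. It does not say that those doing the surveys see earlier allocations, that they set the order of entry, or who runs the allocation program. A reader might infer from the open delivery that staff know the past allocations and choose who comes next, so that half of this trial's allocations are guessable and can be steered. The text does not support that inference. The 49.7% is a ceiling for one person with complete knowledge, and even then half the guesses are wrong.

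The route is also narrower than in many open trials. Consent and the baseline survey come before randomisation, so women cannot be turned away once an arm is known. The intention item sits inside that survey, so a caller choosing whom to contact next does not yet have the answer. Acting on it would mean delaying randomisation after the survey, which the article neither describes nor excludes. An outside statistician, computerised allocation and blinded outcome review are real safeguards. Details of concealment may sit in the full protocol, and their absence from an article is no fault.

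All of this stands, and it makes the point conditional and small. It does not remove the point, because a single disclosed block length is something the article itself fixes. It is also fair to object that smaller varying blocks would raise the average hit rate, and the fix below takes account of that.

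**Conclusion.** The point holds in a limited form. The article fixes and discloses one block length in a trial with visibly different arms. **If** someone involved in recruitment or survey work can follow all earlier allocations and knows the block boundaries, that person's hit rate is up to about 50% against 33% by chance, with about 9% of places (about 55 of 600) certain. With partial sight the rate falls towards 33%: about 40% when half are seen.

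Whether this could bias the trial rests on two things the article leaves open: who sees the allocations, and who influences the order in which consented women are surveyed and randomised. There is no evidence that allocation was or would be steered. This is a desirable improvement, not a flaw that undermines the design.

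**What to change.** In the Randomization section, replace the rule of balance after every 15 participants with randomly varying block sizes, mostly no smaller than the current 15. Either 15/18/21 or 12/15/18 would do. The independent statistician should generate the list, and neither the sizes nor the running tally should be disclosed to recruiting, survey or promotora staff. The section should describe the blocks only as randomly varying and leave the sizes to a restricted document. It would help to add that the arm is released only after the baseline survey is complete.

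Sizes such as 6 and 9 should be avoided: a 6/9/12/15 mix also cuts certain places to about 1.5%, but raises the average hit rate to about 52%. Withholding the scheme matters at least as much as varying it.

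The cost is a new computer-generated list and a sentence or two of text. Arm sizes may differ by a few women if recruitment stops mid-block, which is of little consequence against 200 per arm. The planned tests and sample size are unaffected.
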